#### Indoor residual spraying (IRS)

Indoor residual spraying with propoxur will be carried out at three times during the study period in the LLINs + IRS and IRS alone arms. Spraying will be done once a year prior to the peak transmission season at the beginning, the middle and before the end of the trial, following the national spraying operation guidelines [43] and WHO operation manual guidelines [54]. Propoxur (isopropoxy-phenyl methylcarbamate) is highly effective against mosquito vectors for more than 3 months at a dosage of 2 g/m^2^ in the form of a water-dispersible powder (WP) [54], and will be acquired from the state-owned Adami Tullu Pesticide Processing Share Company located in the study district. Propoxur 50 % WP contains 2 g of active ingredient and is packaged in 400 g sachets, and two sachets will be mixed with 8 L of water. Preliminary findings using the WHO susceptibility tube tests in 2013 showed a 100 % susceptibility of *An. arabiensis* and *An. pharoensis* to propoxur (*MalTrials* unpublished pilot data).

We will use the average surface area measurement per unit structure (110 m^2^) to be sprayed by a spray man per day to calculate the correct amount of insecticide required for the spraying. All IRS operations will be carried out in collaboration with the DHO as per the recommendations of the national guidelines [43]. A 6-day training on spraying operation will also be given for locally recruited spray men and supervisors. The spraying teams will be organized by squads of four spray personnel and a porter, and supervised by a squad leader. The DHO malaria focal persons and HEWs will be used to organize, follow-up, and supervise the daily activity of spray teams, and a spray equipment and personnel protective clothing will be obtained from the DHO.

Approximately 12 houses will be sprayed by each spray operator per day using an 8-liter Hudson X-pert (HD Hudson Manufacturing Company, Chicago, IL, USA). Prior to spraying, a community sensitization will be performed to inform residents in regard to the safety, purpose and time of spraying. On the day of the IRS operation, all targeted households will be informed about the schedule, purpose and requirements of the spraying. The householders will be requested to prepare and vacate the house before spraying, and household items such as water, food and cooking utensils will be removed from the house. Household members will be allowed to enter the sprayed house after 30 minutes, and be requested to clean the floor and bury or burn the dirt. The householders will also be requested not to wash, paint or re-plaster the sprayed walls until at least the end of the main transmission season.

### Study endpoints

The primary health outcome measure is malaria incidence determined by the detection of *P. falciparum* or *P. vivax* by rapid diagnostic tests (RDTs) in patients with a fever or having a history of fever within the previous 48 hours upon arrival at health posts by passive case detection (PCD). The sensitivity and specificity of the RDTs compared with the results of the light microscopy will be determined. The secondary health outcome measure is mean Hb concentration in children under the age of 5 years, which is measured using a portable photometer (HaemoCue®, Ångelholm, Sweden) at the end of each transmission season through community-based house-to-house visits.

The primary outcome measure of the economic evaluation is the total cost of the interventions. The secondary outcome measures are the direct and indirect costs of the intervention from both the provider and societal perspectives, which includes Disability- adjusted Life Years (DALYs) and the number of malaria cases averted by each intervention.

The primary entomological outcome measure is malaria transmission expressed as EIR, estimated as the mean number of sporozoite infective bites/person/year. The secondary entomological outcome measures are the mean number of *An. arabiensis*/light trap/night, and mean number of *An. arabiensis* in spray catches/night inside houses.

### Sample size

#### Malaria incidence and anemia prevalence

Sample sizes were calculated based on unpublished epidemiological data collected in a baseline pilot study in villages adjacent to Lake Zeway during September to December 2013. The sample size for the primary endpoint, the incidence of malaria, was calculated using methods for cluster randomized trials [55] that take into account the intra-cluster correlation coefficient (ICC), incidence rate, the expected effect and the power of the study. Using a baseline malaria incidence rate of 7.85 per 10,000 person-weeks and the coefficient of variation between clusters within each group, we used *k* = 0.27 in the sample size estimation (*MalTrials* unpublished pilot data). Thirty-five households (approximately 175 people) per cluster will be followed up for 116 weeks, with 44 clusters achieving a 90 % power to detect a 25 % reduction in the malaria incidence rate in the LLINs + IRS arm compared to LLINs alone or the IRS only arm, using a two-sided 5 % significance level. We plan to follow approximately 1540 households with an estimated 7800 people in each arm of the trial (Fig. 2). Overall, the trial will cover over 31,000 people from approximately 6100 households. The proposed sample size is also assumed to suffice in terms of having the power to detect a mean reduction between the study arms of 0.5 mg/ml Hb concentration in children under 5 years of age.

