The WHO age-adjusted cut-off for Hb will be used to classify anemia in children [71]. For children between 6–59 months of age, a normal Hb level is defined as Hb of 11.0 g/dl or greater and as mild at 10.0–10.9 g/dl. Moderate anemia is defined as children with an Hb level of 8.0–10.9 g/dl while severe anemia is defined as an Hb level of less than 8.0 g/dl. At a community level, a prevalence of anemia will be stated to be severe if over 40 % of the children are anemic (combining mild, moderate and severe) and moderate if the prevalence is 20–39.9 %. We will measure the weight and height of all children under the age of 5 years, and calculate the anthropometric indices such as weight for height, height for age, and weight for age. Both malaria and anemia prevalence data will be compared in the intervention and control clusters using multilevel mixed-effects logistic regression models, taking clustering effects into account.

Cost-effectiveness, expressed as an incremental cost-effectiveness ratio (ICER), will be calculated for each outcome and arm using standard DALY weights. The interventions will be ranked according to cost-effectiveness, whereas inequality in terms of health outcomes, will be measured by the Gini coefficient and the concentration index [72].

The agreement between the two mosquito collection methods, HLC and light traps, in assessing mosquito sampling efficiency will be calculated by a parametric approach based on an analysis of variance and simple graphical methods. Indoor and outdoor *Anopheles* densities will be compared among the study arms using a one-way analysis of variance (ANOVA) if data are normally distributed or using a Mann-Whitney *U* test if data are non-normally distributed.

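### The haemoglobin difference is printed as 0.5 mg/ml (0.05 g/dl), several times smaller than this sample can plausibly detect, and no named model fits the mean-Hb endpoint

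*Protocol article*

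**What the plan says.** The protocol article, Sample size (Malaria incidence and anemia prevalence), derives the trial size from malaria incidence: "44 clusters achieving a 90 % power to detect a 25 % reduction in the malaria incidence rate", "using a two-sided 5 % significance level". It then extends the claim to Hb in children under 5 without a calculation: "The proposed sample size is also assumed to suffice" for "power to detect a mean reduction between the study arms of 0.5 mg/ml Hb concentration".

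Study endpoints defines the outcome that this claim serves: "The secondary health outcome measure is mean Hb concentration in children under the age of 5 years". It is the only secondary health outcome listed there. The secondary objectives name both a better Hb concentration and less anaemia in children under 5.

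Elsewhere Hb is given in g/dl. Epidemiological data collections sets the anaemia cut-off at 11.0 g/dl, and the Analytical plan repeats it: "a normal Hb level is defined as Hb of 11.0 g/dl or greater". The one model that the Analytical plan names for the Hb data is for the binary outcome: "anemia prevalence data will be compared in the intervention and control clusters using multilevel mixed-effects logistic regression models". The same section says in general terms that primary and secondary outcomes will be compared between arms, without naming a method for mean Hb.

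**The concern.** A difference of 0.05 g/dl is half of the 0.1 g/dl step in which the article writes its own anaemia cut-offs. A sample sized for a 25% fall in malaria incidence would not be expected to resolve a mean shift that small. If the figure is wrong as printed, the only design justification given for the sole secondary health outcome is wrong too, and a reader cannot tell what Hb effect the trial was planned to show.

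There is a second, smaller mismatch. The endpoint and the power statement both concern a mean, but the named model concerns a proportion. A logistic comparison of children below 11.0 g/dl does not estimate the quantity that the power statement describes, and it uses less of the information in the Hb measurements.

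**Working it through.** **Unit.** 0.5 mg/ml × 100 ml/dl = 50 mg/dl = 0.05 g/dl.

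**Plan's own figure.** It cannot be reproduced, because the article gives no Hb SD, ICC, number of children or power level. The *k* = 0.27 in the same section is for malaria incidence, not Hb.

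**Inputs from the article.** 44 villages per arm, about 175 people per village, about 7800 people of all ages per arm, two-sided 5% level (stated for malaria incidence, taken to apply to Hb).

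**Assumed inputs.** n = 15 to 30 measured children per village (15/175 = 9% to 30/175 = 17% of residents), SD 1.2 to 1.8 g/dl, ICC 0.01 to 0.10, and 90% as the target power, as for the primary endpoint.

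**Formulas.**
- SE = SD × √[ 2 × (1 + (n − 1) × ICC) / (44 × n) ]
- Power for a difference d = Φ(d/SE − 1.96) + Φ(−d/SE − 1.96)
- Difference detectable with 90% power = (1.960 + 1.282) × SE = 3.24 × SE

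**Central case** (n = 26, SD 1.5, ICC 0.05). Design effect = 1 + 25 × 0.05 = 2.25. SE = 1.5 × √(2 × 2.25 / 1144) = 0.094 g/dl.

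| Case | SE (g/dl) | Power for 0.05 g/dl | Power for 0.5 g/dl | Detectable at 90% power (g/dl) | Multiple of 0.05 |
|---|---|---|---|---|---|
| Most favourable: n = 30, SD 1.2, ICC 0.01 | 0.053 | 16% | over 99% | 0.17 | 3.4 |
| Central: n = 26, SD 1.5, ICC 0.05 | 0.094 | 8% | over 99% | 0.30 | 6.1 |
| Least favourable: n = 15, SD 1.8, ICC 0.10 | 0.154 | 6% | 90% | 0.50 | 10.0 |

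**Can any realistic input rescue 0.05 g/dl?** Three checks, each generous to the plan:
- Ignore clustering and take SD 1.0 g/dl. Children needed per arm = 2 × 3.24² × 1.0² / 0.05² = 8,406 with unrounded normal quantiles. That exceeds the 7800 people of all ages in an arm.
- Take 1170 children per arm (15% of 7800, assumed) and no clustering. The SD would have to be 0.05 / (3.24 × √(2/1170)) = 0.37 g/dl.
- Table 1 schedules three anaemia surveys. Pool them as if independent (3 × 1170 = 3510 observations per arm), with SD 1.0 and no clustering. The detectable difference is 3.24 × √(2/3510) = 0.077 g/dl, still above 0.05.

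**Analysis.** Side by side: Study endpoints declares a mean, the sample size section claims power for a mean, and the Analytical plan names a model only for a prevalence. Nothing in the article names a model for the mean.

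**The case against.** The strongest reply is that this is a slip of units with no effect on the design. If 0.5 g/dl was meant, the sample is adequate, and the 95% confidence intervals promised for all estimates would show the actual precision. Much of this stands. It limits the harm, and it means that a misreading of a null Hb result is a possibility rather than something the documents imply. It does not make the printed figure right, and 0.5 g/dl appears nowhere in the article.

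Four stronger readings are tempting and are not supported:
- A reader might infer that the printed figure is ten times smaller than the sample can detect. Ten is the ratio of 0.5 to 0.05 g/dl. The ratio of the detectable difference to the printed one is about 6 in the central case and reaches ten only in the least favourable corner of the assumed range.
- A reader might infer that mean Hb will receive only a yes/no analysis. The Analytical plan promises a comparison of all secondary outcomes, and a model for mean Hb may sit in an analysis plan that is not shown. Anaemia is also part of the stated objective, so the logistic model has a proper use.
- A reader might infer that the hypothesis is reversed, because the sentence speaks of a reduction while the objective is to improve Hb. Under a two-sided test the power is the same either way, and the secondary objectives give the direction correctly. This is loose wording.
- A reader might infer that a promised power level is missed. The article states no numerical power for Hb, only an assumption that the sample is enough.

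**Conclusion.** The point holds in this limited form. As printed, the Hb statement is wrong: 0.5 mg/ml is 0.05 g/dl, for which power is about 6 to 16%, while the detectable difference at 90% power is about 0.2 to 0.5 g/dl. The range rests on assumed SD, ICC and children per village, so no exact multiple can be asserted. The conclusion that 0.05 g/dl is out of reach does not depend on the exact choice, since it fails even without clustering at SD 1.0 g/dl. A slip for 0.5 g/dl is the likely explanation and would leave the design adequate on these assumptions, but only the sponsor can confirm it.

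The analysis point is secondary: the declared endpoint and the only named model do not match. That is a mismatch to be closed, not proof that mean Hb goes unanalysed. The sample size for malaria incidence is untouched. The correction should be made, but it does not threaten the trial.

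**What to change.** 1. Have the sponsor confirm the intended Hb difference and correct the figure, to 0.5 g/dl (5 mg/ml) if that is what was meant. Word it as a difference in mean Hb between arms.
2. Restate the power for that difference with the SD, ICC, number of children per village and significance level used.
3. Name a linear mixed model for mean Hb with a village random effect, and with a child effect where the same child is measured in more than one survey. Keep the logistic model for anaemia prevalence as supportive.

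The cost is one corrected figure, one line of inputs and one sentence of analysis text. If 0.5 g/dl is confirmed, no change to sample size or data collection follows on the assumptions above.

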#### Economic evaluation

The sample size calculated for malaria incidence is also assumed to suffice for the economic evaluation of the cost of interventions. The sample size for the cost of illness study (at the patient level) is calculated using a single population mean formula. Hence, 260 participants will be enrolled into the study from the passively detected malaria patients using a consecutive sampling technique.

#### Entomological study

We aim to calculate the sample size for the entomological collections based on the pilot entomological studies. In a West African study with a 90 % power and 5 % significance level, it was advised to sample eight houses from each of 15 clusters of the study arms, but the mosquito density was lower [56]. A total of 16 villages (four per arm) will be randomly selected for entomological study, in which indoor host-seeking mosquitoes will be collected by CDC light traps from four houses per arm, indoor resting mosquitoes from 16 houses per arm using pyrethrum spray collection and outdoor resting mosquitoes from four artificial pit shelters per arm of the study.

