#### Entomological data collections

The results of trials from countries where *An. gambiae* s.s. is the dominant vector might not be fully applicable in countries such as Ethiopia, where *An. arabiensis* is the main vector. The latter vector is less affected by mosquito nets, and is more exophilic and less anthropophilic [58]. Estimating the human biting rate (HBR) of mosquitoes is important for a risk assessment of malaria transmission. The Centers for Disease Control and Prevention (CDC) light traps, used in many studies, are only a proxy measure to estimate HBR. Human landing catches (HLC) are a more direct way to estimate HBR, and are often considered the “gold standard” [59]. Recent research showed that light trap collections placed close to inhabited mosquito nets may not be a reliable method of assessing human biting rates [60].

The CDC light traps and HLC will be compared before starting the trial. Since HLC cannot be used for community-wide mosquito collections due to ethical and logistical drawbacks, CDC light trap collections will be calibrated with HLC locally in order to estimate an operational conversion factor for calculating the HBR and EIRs. Mosquito collections will be carried out during the malaria transmission season following interventions.

The CDC light traps, pyrethrum spray sheet catches and artificial pit shelters will be employed to collect mosquitoes and assess their biting behavior, indoor and outdoor resting densities. Houses will be randomly selected from a computer-generated list and the person will be blinded to the arms and houses. For CDC light traps and pyrethrum spray catches, the number of houses will be four and 16 from each arm, respectively, while four pit shelters in each arm will be constructed. Mosquitoes will be collected weekly from August to November each year, and will be identified to species using a morphological key [61]. Previous studies indicated the presence of *An. arabiensis* as the only species of the *An. gambiae* complex in the study area [50]; however, for reconfirmation purpose a species-specific polymerase chain reaction (PCR) will be applied [62].

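### With light traps in four houses per arm, differences of 25 to 50% in EIR, the primary entomological outcome, are unlikely to be detectable under stated assumptions on infective catches

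*Protocol article*

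**What the plan says.** Under Study endpoints: "The primary entomological outcome measure is malaria transmission expressed as EIR, estimated as the mean number of sporozoite infective bites/person/year". The secondary objectives list EIR among the parameters to be compared between the combination and each single intervention, and the Discussion part of the abstract poses it as a research question. Mean An. arabiensis per light trap per night is a secondary entomological outcome.

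On sampling, the Entomological study part of the sample-size section states: "A total of 16 villages (four per arm) will be randomly selected for entomological study", and that "indoor host-seeking mosquitoes will be collected by CDC light traps from four houses per arm". The Entomological data collections section gives "For CDC light traps and pyrethrum spray catches, the number of houses will be four and 16 from each arm, respectively", plus four pit shelters per arm, and "Mosquitoes will be collected weekly from August to November each year". Light-trap catches are to be converted to biting rates and EIR by a local calibration against human landing catches; its value is not given. Females from every collection method, except blood-fed ones, are tested for sporozoites.

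The sample-size section opens with "We aim to calculate the sample size for the entomological collections based on the pilot entomological studies". It cites a West African recommendation of eight houses in each of 15 clusters, adding that mosquito density was lower there. The Analytical plan compares Anopheles densities by one-way ANOVA or a Mann-Whitney test and mentions no allowance for village, although it does so for malaria and anemia prevalence.

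**The concern.** EIR is a biting rate multiplied by a sporozoite-positive fraction. However many mosquitoes are trapped, a comparison of EIR carries little information when few of them are infective. The stated malaria incidence is low, so infective bites are probably rare, and four traps per arm sample few person-nights.

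With very small counts, a chance zero in the combination arm can be read as interrupted transmission, and similar small counts as no added benefit. Neither reading would be supported, and the trial is meant to inform national and global malaria policy.

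**Working it through.** The documents give no power, effect size, mosquito density or sporozoite rate for the entomological sample, so there is no stated figure to reproduce. The check asks what the stated sampling and incidence imply.

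**Trap-nights.** August to November is 122 nights, or 17.4 weeks. Three seasons (2014 to 2016) give 4 × 17.4 × 3 ≈ 209 per arm. Nets went out on 1 to 5 October 2014; counting only October and November of that year gives 4 × (8.7 + 17.4 + 17.4) ≈ 174.

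**Incidence.** "Using a baseline malaria incidence rate of 7.85 per 10,000 person-weeks": 7.85/10,000 × 52 = 0.041 per person-year.

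**Assumptions.** A share p of infective bites becomes a detected case, p from 0.02 to 0.50. One trap-night equals one person-night of exposure.

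**Expected infective light-trap catches per arm.**
- EIR = 0.041/p, so 2.0 (p = 0.02) to 0.08 (p = 0.50) per person-year.
- With all transmission placed in the 122 sampled nights, which favours the plan: 209 × EIR/122 = 3.5 to 0.14. The chance of no positive at all, exp(−mean), is 3% to 87%.
- The pilot rate was measured from September to December, so it can also be read as an in-season weekly rate: 209 × 0.000785/(7p) = 1.2 to 0.05.
- More favourable readings take p = 0.005 (for example, 2% of bites infecting and a quarter of infections detected) with the in-season rate. Year-round trapping, as Table 1 could be read (about 505 trap-nights), gives 505 × 0.000785/(7 × 0.005) ≈ 11. A trap representing five sleepers over 209 nights gives ≈ 23.

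**Positives needed.** For a rate ratio r, comparator-arm positives = (z_α/2 + z_β)² × (1 + 1/r)/(ln r)². At two-sided 5%, 80% power for r = 0.5 needs 2.80² × 3/0.48 = 49. At 90% power, reductions of 25%, 50% and 80% need about 296, 66 and 25.

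**Power**, exact conditional binomial comparison of two Poisson counts, two-sided 5%, no clustering:

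| Expected positives, comparator arm | 25% reduction | 50% | 80% |
|---|---|---|---|
| 3.5 | 2% | 3% | 8% |
| 11 | 6% | 20% | 62% |
| 17 (five times 3.5) | 9% | 32% | 84% |
| 23 | 11% | 43% | 94% |

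**With clustering.** The Hayes-Bennett formula with c = 4 villages and m expected positives per arm gives z_β = √{3(1 − r)²/[(1 + r)/(m/4) + k²(1 + r²)]} − 1.96. Using k = 0.27, borrowed from malaria incidence, m = 23 gives 10%, 31% and 74%.

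**Density instead.** If counts are large enough for Poisson noise to vanish, the first term in the denominator drops out. At k = 0.27, power is 25% for a 25% reduction and 82% for a halving; at k = 0.5, it is 10% and 34%. These are upper bounds, because k for mosquito density is not given.

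**What a zero would mean.** The exact two-sided 95% upper limit for no positives is −ln(0.025) = 3.69. Over 209 trap-nights that is 3.69/209 × 122 = 2.2 infective bites per person per four-month season, above the highest EIR in the 2% to 50% range. A zero would not show interruption.

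**The case against.** Much of the opposing case stands.

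- A reader might infer that the incidence figure by itself proves a catch of only zero to four infective mosquitoes per arm. It does not: the count depends on the bite-to-case share, the trap conversion factor and the number of trap-nights, and the first two are not in the documents. Stacking the most generous readings (p = 0.005, year-round trapping and five sleepers) gives about 5 × 11.3 ≈ 57, enough for 80% power to detect a halving before clustering. That needs an extreme p and trapping outside the months the text states.
- Spray catches from 16 houses and four pit shelters per arm also feed the sporozoite fraction, so the light-trap positives do not alone fix the precision of EIR. The yield of those collections is not given, so the gain cannot be sized; a fivefold gain on 3.5 is the 17 row above. The biting-rate factor still comes from four houses per arm.
- Eight houses in 15 clusters is 120 per arm against four, but a 30-fold sampling deficit cannot be inferred. The protocol notes the lower density there, and the cited study's outcome, target effect and nights per house are not shown.
- The absence of a power statement is not a fault here: a condensed article may leave the pilot-based calculation to the full protocol.
- Density comes from the same four houses and villages per arm, and the protocol itself warns that light traps near occupied nets may measure biting rates unreliably. Changing the entomological comparison in an ongoing trial also invites a charge of outcome switching.

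The last point limits the remedy and requires a documented amendment. It does not make the EIR comparison informative.

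**Conclusion.** The point holds conditionally. With four light-trap houses and villages per arm, and on the stated assumptions, about 0.1 to 3.5 infective light-trap catches per arm are expected, or 11 to 23 on more favourable readings. From 3.5 to 23, power for a 25 to 50% difference in EIR is about 2% to 43% before clustering. An effect near 80% might be seen at the top of that range: 94% without clustering, 74% with four villages and k = 0.27. It is therefore too strong to say that EIR can never serve as the entomological outcome; the supportable statement is that moderate differences are unlikely to be resolved. Entomology is a secondary objective, and the primary malaria-incidence comparison is unaffected.

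**What to change.** 1. Report EIR per arm as an estimate with exact Poisson-based limits, including an upper limit where no positives are found. State which collections supply the sporozoite data. Do not conclude that EIR differs, is equal or is interrupted from a handful of positives.
2. Base the between-arm entomological inference on An. arabiensis per light trap per night, analysed with village as the unit in place of the ANOVA or Mann-Whitney test without allowance for village.
3. Align the EIR question in the abstract's Discussion and in the secondary objectives with this.
4. Record the change as a dated amendment made without sight of arm-level data. Table 1 places the 2014 and 2015 collection seasons before the January 2016 publication, so the amendment should say what had been seen by then.

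The cost is a text and analysis change, with no extra trapping. The entomological claim moves from transmission to vector density, and density remains limited by four villages per arm: a halving is within reach only if between-village variation is modest (82% power at k = 0.27, 34% at k = 0.5, both upper bounds).
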